**Fig. 1 Fig1:**
[figure not shown]
Overview of study design from recruitment to follow-up

### Recruitment

Individuals will be recruited from both the community, with advertisements placed in community centers and newspapers in Greater Vancouver, and from the University of British Columbia Hospital Clinic for Alzheimer’s Disease and Related Disorders. All individuals who receive care at the clinic have the option to sign a consent form providing access to their records for research purposes and indicating their willingness to be approached for research studies. Individuals interested in participating will be screened by telephone to check for eligibility based on our inclusion and exclusion criteria, and the Physical Activity Readiness Questionnaire for Everyone (PAR-Q Plus) [44], a screening measure of physical readiness for exercise. Research staff will invite eligible participants to attend a consent and screening session, either over the phone or in-person, during which details of the study will be provided.

### Time frame

Participant enrollment began on November 13, 2017, and the final assessment is anticipated to be completed by December 2023. The COVID-19 pandemic impacted recruitment for much of 2020. As of May 25, 2022, 176 individuals (81% of the target sample) have been recruited and randomized.

### Eligibility

#### Inclusion criteria

We will include community-dwelling females and males who meet the following inclusion criteria: (1) aged between 65 and 85 years; (2) have subjective memory complaints, defined as the self-reported feeling of worsening memory, as determined by a standard question [45]; (3) have baseline MoCA score of < 26/30 [46]; (4) have a Mini-Mental State Examination (MMSE) score > 22 [47] and a Clinical Dementia Rating score < 1.0 [43]; (5) do not have any significant impairment in daily function as indicated by a score of > 6/8 on the Lawton and Brody Instrumental Activities of Daily Living Scale [48]; (6) score < 5/15 on the Geriatric Depression Scale (GDS) [49]; (7) completed high school education; (8) live in their own home; (9) read, write, and speak English with acceptable visual and auditory acuity; (10) not expected to start, or are stable, on a fixed dose of anti-dementia medications (e.g., donepezil, galantamine); (11) provide a signed and dated informed consent document; (12) able to walk independently without an aid; (13) in sufficient health to participate in the exercise programs, based on their medical history, the PAR-Q Plus [44], and written approval by their family physician (if required); and (14) have the capacity to comply with the scheduled assessments and exercise sessions.

#### Exclusion criteria

We will exclude individuals who are (1) engaged in moderate-intensity aerobic exercise > 60 minutes per week, in the 3 months prior to study entry; (2) engaged in progressive resistance training > 1×/week in the 3 months prior to study entry; (3) diagnosed previously with dementia of any type; (4) clinically suspected to have neurodegenerative disease as the cause of MCI that is not Alzheimer’s disease, vascular cognitive impairment, or both (e.g., multiple sclerosis, Parkinson’s disease, Huntington’s disease, frontotemporal dementia); (5) at high risk for cardiac complications during exercise or unable to self-regulate activity or to understand recommended activity level; (6) diagnosed by their family physician with clinically important peripheral neuropathy or severe musculoskeletal or joint disease that impairs mobility; (7) on a new or recent (i.e., less than 3 months from study entry) or changed dose of medications that may negatively affect cognitive function, such as anticholinergics (i.e., typical and atypical antipsychotics) and anticonvulsants (e.g., gabapentin, valproic acid); (8) on any hormone therapy (estrogen, progesterone, or testosterone) in the last 24 months; or (9) planning to participate, or already enrolled in, a concurrent clinical drug or exercise trial.

A subset (~40%) of right hand-dominant participants will undergo magnetic resonance imaging (MRI) scanning. We will exclude participants who do not meet the specific scanning requirements of the UBC MRI Research Centre or do not provide consent. Specifically, participants will be excluded from the MRI scanning if they have any of the following: pacemaker, brain aneurysm clip, cochlear implant, surgery or tattoos within the past 6 weeks, electrical stimulator for nerves or bones, implanted infusion pump, history of any eye injury involving metal fragments, artificial heart valve, orthopedic hardware, other metallic prostheses, any blood vessel filter, coil or catheter, ear or eye implant, bullets, or other metallic fragments.

### Sample size considerations

The planned sample size was determined with the aim of testing the main effects of AT and RT on changes in cognitive function, as assessed by the ADAS-Cog-Plus [50]. In computing the required sample size, we used G*Power and the sample analytic model in the statistical analyses. Unpublished data from a separate set of 96 older adults with MCI from our laboratory estimated that the correlation between baseline ADAS-Cog-Plus and the same measure collected 6 months later was approximately 0.80 [51]. This value was used to calculate the assumed residual variance in the analysis of covariance (ANCOVA) model of 0.36 (i.e., 1 − 0.80^2^). With a targeted enrolment of 216 individuals and accounting for an overall dropout of 15% (assumed to impact each intervention arm equally), we will have a power of 0.80 to detect a standardized mean difference (SMD) of 0.27 for the effect of AT or RT on cognitive function with a two-tailed alpha of 0.05 applied to each comparison [9]. The SMD of 0.27 concurs with findings from recent meta-analyses [9, 52, 53]. To detect an interaction between AT and RT with 0.80 power, the true effect size of 0.53 is required. Figure 2 depicts the 3 planned primary comparisons to examine the main and interaction effects of AT and RT.

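### The stated detectable effects (0.27 main, 0.53 interaction) do not follow from the sample size inputs, which give 0.25 and 0.50 at 0.80 power; the discrepancy is conservative

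*Protocol article*

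**What the plan says.** The protocol article, under Sample size considerations, gives every input:

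- Size and loss: 216 enrolled, with "an overall dropout of 15% (assumed to impact each intervention arm equally").
- Correlation: "the correlation between baseline ADAS-Cog-Plus and the same measure collected 6 months later was approximately 0.80".
- Residual variance: this correlation leads to "the assumed residual variance in the analysis of covariance (ANCOVA) model of 0.36", which is 1 − 0.80².
- Type I error: "with a two-tailed alpha of 0.05 applied to each comparison". The Statistical analyses section confirms that alpha is uncorrected and that month 6 is the primary endpoint.
- Allocation: 1:1:1:1 in a 2 × 2 factorial (Randomization section).

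Two outputs are stated. For the main effects, "we will have a power of 0.80 to detect a standardized mean difference (SMD) of 0.27 for the effect of AT or RT". For the interaction, "To detect an interaction between AT and RT with 0.80 power, the true effect size of 0.53 is required".

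**The concern.** The paragraph is the article's justification for 216 participants, and it presents 0.27 and 0.53 as results of the inputs listed beside them. A reader who puts those inputs into a standard ANCOVA power calculation gets smaller detectable effects. The two stated figures stand in roughly the 1:2 ratio expected between a main effect and an interaction in a balanced factorial (0.53/0.27 = 1.96). That suggests one common input differing from what is written, more than a slip in a single number. At stake is whether the power statement for the primary comparisons can be reproduced and cited as it stands.

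**Working it through.** **Inputs.** N analysed = 216 × 0.85 = 183.6, so 91.8 per level of each factor and 45.9 per cell. Residual SD = √0.36 = 0.60 on the SMD scale. Two-sided alpha 0.05, power 0.80. The article does not define the interaction effect; I take it as the difference of differences between cells, which matches the 1:2 ratio above.

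**Standard errors.**
- Main effect (half against half): 0.60 × √(4/183.6) = 0.0886.
- Interaction: 0.60 × √(16/183.6) = 0.1771.

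**Attempt to reproduce the stated figures, normal approximation.** The multiplier is 1.960 + 0.842 = 2.802.
- Main effect: 2.802 × 0.0886 = 0.248 (stated 0.27).
- Interaction: 2.802 × 0.1771 = 0.496 (stated 0.53).

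**Same check with the 1-df F test** (denominator df N − 6; noncentrality d²N/(4 × 0.36) for a main effect and d²N/(16 × 0.36) for the interaction):

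| | Stated at 0.80 power | Recomputed at 0.80 power | Power at the stated effect |
|---|---|---|---|
| Main effect of AT or RT | 0.27 | 0.249 | 0.858 |
| AT × RT interaction | 0.53 | 0.499 | 0.845 |

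Rounding does not explain the gap. Taking 180 or 184 analysed gives 0.252/0.504 or 0.249/0.498. At the lower rounding limits of the stated effects, power is 0.845 at 0.265 and 0.838 at 0.525, still above 0.80.

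**In reverse.** By the F test, 0.80 power at 0.27 needs 157 completers, and 157/0.85 rounds up to 185 enrolled. At 0.53 for the interaction it needs 163 completers, and 163/0.85 rounds up to 192 enrolled. The plan enrols 216.

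**A check on the method.** The same section states power above 0.90 for sex-by-exercise interactions of 0.65 and 0.75. The interaction formula above gives 0.95 and 0.99, so that statement reproduces. Only the 0.27 and 0.53 pair does not.

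**What would give the stated pair** (F test, one input changed at a time):

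| Change | Main | Interaction | Rounds to 0.27 and 0.53? |
|---|---|---|---|
| Power 0.85 | 0.267 | 0.534 | yes |
| Loss 25% (162 analysed) | 0.266 | 0.532 | yes |
| Residual variance 0.41 | 0.266 | 0.532 | yes |
| No loss (216 analysed) | 0.230 | 0.460 | no |
| Two-sided alpha 0.025 | 0.275 | 0.550 | no |

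The three changes that work each contradict an input the section states.

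**The case against.** The strongest counter-argument is that the section never says dropouts are removed from the analysis. The Statistical analyses section plans intention-to-treat with multiple imputation, so all 216 could be counted, with the 15% loss entering as a dilution of the effect. The main effect then reproduces: 0.2298/0.85 = 0.270, with power 0.799 at 0.27. But the article does not describe a dilution, and the interaction becomes 0.4596/0.85 = 0.541, which does not round to 0.53. This reading recovers one figure and not the pair.

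It can also be said that the correlation is only approximate, from 96 people, and that a value of 0.77 would give 0.265 and 0.531. This shows how sensitive the result is, but the section fixes the residual variance at 0.36, and 0.77 would make it 1 − 0.77² = 0.41.

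The objection that the matter is small stands. The differences are 0.02 and 0.03 in SMD, both on the safe side, and no decision on design, alpha or enrolment turns on them.

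**Conclusion.** The stated detectable effects do not follow from the stated inputs. On those inputs 0.80 power corresponds to 0.25 for each main effect and 0.50 for the interaction; power is about 0.86 at 0.27 and about 0.85 at 0.53. This rests on dropout reducing the number analysed to about 184, on the interaction being a difference of differences, and on month 6 being treated as a single-time-point ANCOVA.

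A reader might infer more than the document supports:

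- *That the trial is undersized.* It is not. The error runs the other way, and 216 exceeds the 185 and 192 enrolled that the stated effects would need at 15% loss.
- *That a loss near 25% or a variance near 0.41 must have been assumed without being stated.* Power of 0.85, with dropout and variance untouched, explains the pair equally well. The article does not settle which applies.
- *That the sponsor cannot tell how much loss the trial can absorb.* The planned loss is stated as 15%, and at that loss power exceeds 0.80 for both stated effects.

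This is a reporting inconsistency of modest size in the primary power statement.

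**What to change.** If the inputs are as written, restate along these lines: *With 216 enrolled and 15% loss (about 184 analysed), power is 0.80 for an SMD of 0.25 (0.86 for 0.27) for each main effect, and 0.80 for 0.50 (0.85 for 0.53) for the interaction.*

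If 0.27 and 0.53 were the intended detectable effects, check the saved G*Power output and correct whichever of the power (0.85), the dropout or the residual variance was actually used, so that inputs and outputs agree.

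The cost is wording only. Enrolment target, design, alpha and analysis stay as they are.

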**Fig. 2 Fig2:**
[figure not shown]
Schematic representation of the three primary comparisons in the factorial randomized controlled trial design

Our secondary objective is to test whether biological sex moderates the effect of exercise (AT and RT, separately) on changes in cognitive function, as assessed by the ADAS-Cog-Plus. We conducted two meta-analyses [10, 52] and observed an average sex difference, as determined by comparing trials with high versus low proportion of female, in AT (SMD=0.75) and in RT (SMD=0.65) on executive functions and episodic memory. Using these values as estimates of the true effect sizes of the biological sex by exercise interaction effects, a total sample size of 216 (108 men and 108 women) randomly assigned to one of the four conditions will provide greater than 0.90 power with a two-tailed alpha of 0.05 and accounting for an overall dropout rate of 15% (assumed to impact each intervention arm equally).

### Data entry

No personal identifiers will be acquired during data collection. All paper-based data will be stored in locked cabinets and all alphanumeric data will be entered by a trained study personnel who will conduct range checks for data values. All alphanumeric data and neuroimaging will be stored on a secured server hosted by UBC. All data will be deidentified.

### Measurements

There will be three key measurement points: baseline, 6 months (trial completion), and 18 months (i.e., 12-month follow-up). To minimize attrition over the 12-month follow-up, participants will be contacted at 6 months post trial completion to complete a set of questionnaires. Baseline measurements will be obtained prior to randomization. See Fig. 3 for the schedule of all study measures.

**Fig 3 Fig3:**
[figure not shown]
Schedule of enrolment, interventions, and assessments according to the SPIRIT Checklist

#### Consent and screening session

Subjective memory complaints will be determined with one verbal yes/no question: “Do you feel like your memory or thinking is becoming worse?”. Global cognition will be assessed with the MoCA [46] and MMSE [47]. The Lawton and Brody Instrumental Activities of Daily Living Scale and the GDS will also be administered. The Edinburgh Handedness Questionnaire will be administered to assess handedness [54].

#### Descriptors

Standing height in centimeters and mass in kilograms will be ascertained using standardized equipment. General health, demographics, socioeconomic status, and education will be obtained via questionnaire. The Functional Comorbidity Index will estimate the degree of comorbidity associated with physical functioning [55]. The GDS will be used to assess depressive symptoms [49]. The EPIC-Norfolk Physical Activity Questionnaire will measure physical activity levels [56]. Engagement in cognitive stimulating activities will be measured with the Florida Cognitive Activity Questionnaire [57] and the Lifetime Participation in Cognitively Stimulating Activities [58]. The National Adult Reading Test will be used to estimate premorbid intellectual functioning [59]. The Reproductive History Questionnaire will assess reproductive histories of participants [adapted from [60]]. To examine potential genetic moderation of exercise efficacy, we will take a targeted approach for common single-nucleotide polymorphisms that have previously been implicated in cognitive aging and exercise-induced cognitive gains (e.g., BDNF Val66Met polymorphism, APOE4) [11, 61]. DNA will be extracted from whole blood by standard protocol, and genotype will be determined by a TaqMan by-design assay.

#### Primary outcome

Our primary measure will be the ADAS-Cog-Plus [50]. The ADAS-Cog-Plus uses a multidimensional item response theory model to generate a global cognitive score from the 13-item ADAS-Cog [62] and additional standard cognitive assessments. For this trial, we will use the 13-item ADAS-Cog (0-85 points), Trail Making Tests (Parts A and B), Digit Span Forward and Backward, Digit Symbol Substitute Test, animal and vegetable fluency, Rey Auditory Verbal Learning Test, and Clock Drawing test as the input variables into the scoring algorithm. Lower ADAS-Cog-Plus scores represent better cognitive performance; scores range from −1.0 to +1.0 [e.g., −1.0 indicates healthy cognitive functioning, 0.0 indicates MCI, and +1.0 indicates dementia [63]].

#### Secondary outcomes

##### Cognitive function

A battery of computerized and standardized paper and pen neuropsychological tests will be used to assess different cognitive domains. The computerized battery will include the National Institutes of Health Toolbox Cognition Battery [64, 65], a comprehensive neuropsychological battery with normative values. Specifically, we will use its (a) Dimensional Change Card Sort Test to measure set shifting; (b) Flanker Inhibitory Control and Attention Test to measure response inhibition and attention; (c) List Sorting Working Memory Test to measure working memory; and (d) Picture Sequence Memory Test to measure episodic memory. Spatial memory will be measured with a computerized paradigm [66]. The task requires participants to recall the spatial location of one, two, or three dots presented on a computer screen. Reaction time and accuracy will be recorded.

Standardized paper and pen neuropsychological tests will assess executive functions, verbal fluency, visual memory, prospective memory, and visuospatial ability. Specifically, the battery will include the individual components of ADAS-Cog-Plus, such as the 13-item ADAS-Cog, Trail Making Tests (set shifting), Digit Span Forward and Backward (working memory), Digit Symbol Substitution Test (processing speed), animal and vegetable fluency (verbal fluency), Rey Auditory Verbal Learning Test (verbal memory), and Clock Drawing. For the 13-item ADAS-Cog, a change of 3.0 points is a minimally important difference [67]; higher scores on the 13-item ADAS-Cog indicate greater cognitive impairment (range 0–85 points).

In addition, we will administer the Stroop Colour Word Test to assess response inhibition and selective attention [68]. Visual memory will be assessed by the Rey-Osterrieth Complex Figure Test [69]. Prospective memory, the ability to remember and perform an intended action at a specific time in the future, will be assessed by the Prospective Memory Test [70]. We will use the Judgement of Line Orientation to test visuospatial skills [71].

##### Health-related quality of life and wellbeing

We will evaluate health-related quality of life using the EuroQol-5 Domain-5 Level (EQ-5D-5L) [72]. This is a preference-based utility instrument that provides weightings for quality-adjusted life years (QALYs). A QALY is a metric used to assess health-related quality of life that captures both quality and quantity of time spent in a particular health state [73]. The EQ-5D-5L captures 243 unique health states based on the following domains: mobility, self-care, usual activities, pain, anxiety, and depression. A score of zero indicates death while a score of 1 indicates full health. The EQ-5D-5L also consists of a visual analog scale that records the individual’s self-related health on a vertical visual analog scale.

We will evaluate wellbeing using the ICEpop CAPability Measure for Older adults [74, 75]. This assesses wellbeing across five attributes: (1) attachment (love and friendship); (2) security (thinking about the future without concern); (3) role (doing things that make you feel valued); (4) enjoyment (enjoyment and pleasure); and (5) control (independence). A score of zero indicates no capability while a score of 1 indicates full capability.

##### Physical function

Cardiorespiratory fitness will be estimated with the modified Balke submaximal-graded exercise treadmill test [76], with heart rate continuously monitored. Participants will walk on the treadmill at a pre-determined speed (females 4.8 km/h; males 5.3 km/h) until they reach volitional fatigue or 70% of heart rate reserve (HRR). The Short Physical Performance Battery will assess general balance and mobility [77]. Participants are assessed on performance of standing balance, walking, and sit-to-stand. Each component is rated out of 4 points, for a maximum of 12 points. A score of < 9/12 predicts subsequent disability [77]. Participants will also complete the 400-m Walk [78]. Participants will be asked to walk 400 m as quickly as they can without running and time to complete will be recorded.

Muscular strength will be examined separately for the upper and lower body. Upper body strength will be assessed using the bilateral hand dynamometer grip strength test. Lower body strength will be assessed using the Biodex bilateral concentric knee extension and flexion strength test. The peak torque a participant is able to achieve will be recorded for each leg for both concentric extension and flexion. Additionally, lower body strength will be measured with the 30-s sit-to-stand test [79]; participants will be asked to complete as many full sit-to-stands as possible within 30 s.

Body composition will be assessed with a full-body dual-energy X-ray absorptiometry (DEXA) (Hologic, Mississauga, ON, Canada) scan. We will use DEXA-derived total body fat mass (g), total body lean mass (g), and body composition (% of fat and lean mass).

##### Actigraphy measures

Objective measures of sleep quality will be estimated over a 7-day period using the MotionWatch8© wrist-worn actigraphy unit (CamNtech; Cambridge, UK) to estimate sleep duration, latency, and fragmentation. Participants will also be asked to complete the Consensus Sleep Diary each morning [80]. In addition to sleep quality, the MotionWatch8© will also be used to calculate daily physical activity. The number of minutes spent in moderate to vigorous physical activity (>3.0 METs) is compared to the total time spent awake and out of bed to determine the percentage of waking hours each day spent in moderate to vigorous intensity physical activity [81].

##### Questionnaires and falls

Standardized questionnaires will be administered to assess anxiety [82], depression [83], sleep quality [84], sleep apnea risk [85], life space mobility [86], everyday memory [87], mindfulness [88], physical activity [89], sedentary behavior [90], social network [91], social provisions [92], loneliness [93], and health care costs [94]. Falls will be prospectively monitored via monthly calendars. See Table 1 for more details.

**Table 1 Tab1:** Psychosocial assessments and other questionnaires

Name	Description
State and Trait Anxiety Inventory (STAI) [82]	A 40-item questionnaire assessing mood and anxiety.
Center for Epidemiologic Studies Depression Scale (CES-D) [83]	A 20-item questionnaire measuring symptoms associated with depression experienced in the past week.
Pittsburgh Sleep Quality Index (PSQI) [84]	A 19-item questionnaire assessing sleep quality in the previous month using subjective ratings for 7 different components (i.e., sleep quality; sleep latency; sleep duration; habitual sleep efficiency; sleep disturbance; use of sleeping medication; and daytime dysfunction).
STOP Bang Questionnaire [85]	An 8-item questionnaire assessing obstructive sleep apnea risk.
Life Space Questionnaire [86]	A 6-item questionnaire to measure the extent of mobility of older adults.
Everyday Memory Questionnaire (EMQ) [87]	A 28-item questionnaire assessing memory failures over the past 3 months.
Mindfulness Attention Awareness Scale (MAAS) [88]	A 12-item questionnaire assessing mindfulness during daily activities such as conversation, commuting, and eating.
CHAMPS Physical Activity Questionnaire for Older Adults [89]	A 41-item questionnaire assessing weekly frequency and duration of physical activities relevant for older adults.
Sedentary Behaviour Questionnaire (SBQ) [90]	A questionnaire assessing time spent in 9 sedentary behaviors during a weekday and weekend.
Lubben Social Network Scale – Revised (LSNS-R) [91]	A 12-item questionnaire assessing social engagement with family and friends.
Social Provisions Scale (SPS) [92]	A 24-item scale measuring the availability of social support.
UCLA Loneliness Scale [93]	A 20-item scale assessing feelings of loneliness and social isolation.
Health Care Resource Utilization (HRU) [94]	A 10-item questionnaire that asks participants about health care visits, services, and ability to do chores for the calculation of economic burden.

